## Introduction

In Japan, 5.4-6.2 individuals per 100,000 population undergo lower limb amputation annually, whereas the rate is higher in Europe and the United States, ranging from 7.4 to 41.3 per 100,000 population [1]. The causes of amputation include trauma from traffic accidents, tumors, congenital diseases, and peripheral circulatory disorders. Notably, circulatory disorder–related amputations are increasing owing to the rising prevalence of conditions, such as diabetes and arteriosclerosis [2]. In a population-based study of geriatrics with vascular amputations, only 36% achieved successful prosthetic fitting, with advanced age and transfemoral amputation linked to failure [3]. Given the anticipated increase in lower limb amputations due to the aging population, medical and social costs, such as long-term hospitalization, rehabilitation, provision of prostheses, and nursing support, are set to escalate [4]. Therefore, restoring the ability to walk and improving the quality of life (QOL) of individuals with lower limb amputations requires immediate attention.

No established method for training patients to walk following lower limb amputation exists [5]. Traditional rehabilitation protocols after lower limb amputation require approximately 8 weeks for residual limb maturation [6], delaying the start of prosthetic gait training until the maturation period is complete. Furthermore, while active prostheses enable a more normalized gait pattern through neuromuscular control [7,8], passive prostheses are typically restricted to use within 8 weeks postamputation, further slowing the acquisition of a new gait pattern using a prosthetic limb. One of the reasons for the lack of an established method for training patients to walk after amputation is that it takes 6-8 weeks for the stump to mature after amputation, and patients cannot bear weight on the amputated side; therefore, they can only walk on the healthy side. Consequently, training is conducted to strengthen the muscles other than the stump, improve function, manage the condition of the stump, and provide functional training on the stump side [9].

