### Outcomes

All gait evaluations at 2 weeks, 8 weeks, and 6 months postoperatively will be conducted without the use of the HAL device. For the primary outcome, assessment will be conducted at 8 weeks postoperatively to evaluate the short-term effectiveness of early HAL-assisted gait training, which is expected to influence the critical period of initial rehabilitation and prosthetic adaptation. Functional recovery may continue beyond this period, particularly up to 6 months; however, the 8-week period was chosen as the primary end point to capture the immediate impact of the intervention. A 6-month follow-up will provide important secondary data on longer-term outcomes. At each time point, walking ability will be assessed under standard conditions using the residual limb or temporary prosthesis, as applicable. A comprehensive examination of various walking-related factors is necessary; therefore, we will collect the items listed in Table 1 extensively. Among these evaluation items, the 2-minute walking distance [13,14] is set as the primary evaluation item, as it is a general indicator of walking ability and is directly linked to ADL and QOL. Other items will be collected as secondary evaluation items. The Locomo 25 is an assessment tool used to evaluate the condition of locomotive syndrome, which indicates a decline in mobility [15].

**Table 1 table1:** Primary and secondary outcomes.

Assessment item			Description

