**Physical function**			
	2-minute walking distance	Measures the total distance walked in 2 minutes, with pylons placed at 30-m intervals.	
	Bilateral lower limb muscle strength	Measured using μ-Tas (ANIMA Corporation) under isometric contraction conditions.	
	Skeletal muscle mass	Measured using InBody S10.	
	Sensory	Evaluated using a tactile sensory testing device.	
	Range of motion	Assessed using the Tokyo University–style goniometer.	
	Berg Balance Scale	Evaluates balance ability using a validated assessment form.	
	Short Physical Performance Battery	A useful measure combining balance ability and walking performance, assessed using a standard evaluation form.	
	Gait analysis	Measures time to complete the TUG and 10-m walk. Gait pattern is analyzed during the 10-m walk using the PhysiGait (CREACT Co, Ltd) gait analysis system, evaluating step length, stride length, weight distribution, gait speed, etc.	
	Cardiopulmonary function	Maximal oxygen consumption (VO₂ max): Measured using a respiratory gas analyzer.	
	Locomo 25	A questionnaire consisting of 25 items regarding body pain and difficulties in daily activities over the past month. Responses are scored on a 5-point scale (0-4 points per item). Locomotive Syndrome Grade 1: Total score ≥7 points. Locomotive Syndrome Grade 2: Total score ≥16 points.	
	Muscle activity	Electromyography (EMG): Measures muscle activity distribution patterns using a multichannel surface EMG system.	
Activity			BI (Barthel Index), FIM (Functional Independence Measure), FAI (Frenchay Activities Index).
Participation			SF-36, Health Utilities Index, Euro-Qol-5D-5L, Long-Term Care Insurance Certification Level, General Self-Efficacy Scale, WHODAS2.0, Locomotor Capabilities Index (LCI), Prosthetic Evaluation Questionnaire Japan.

All physical function assessments (2-minute walk test) will be conducted without HAL assistance.

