### Statistical Analysis

The target sample size was set at 20 patients scheduled for lower limb amputation. Using JMP version 12 (SAS Institute), the sample size was calculated based on a research design assuming that the 6MWD would improve by a factor of 1.5, referencing previous studies on gait analysis using the HAL [16]. The calculation was performed with α=.05, power=0.80, and a prespecified effect size.

The primary analysis population for efficacy evaluation will be the Full Analysis Set (FAS), whereas the secondary analysis population will be the Per Protocol Set (PPS).

The FAS includes all study participants who have undergone at least one session of HAL-assisted gait training and have had at least one efficacy-related observation thereafter. However, individuals who fail to meet the eligibility criteria will be excluded. The PPS comprises participants from the FAS who have completed HAL-assisted gait training (5 days per week, 30 minutes per day) without major deviations from the study protocol and for whom the primary evaluation item can be assessed.

Statistical analyses will be conducted using SPSS version 30.0 (IBM Corp). The primary evaluation item, the 2-minute walking distance, will be analyzed using the FAS population, and the mean (SD) [or median (minimum-maximum)] will be calculated. Comparisons between preoperative, postintervention, and 6-month postoperative outcomes will be performed using a 1-way ANOVA or the Kruskal-Wallis test, with a 2-sided significance level of 5%, and a 95% CI will be calculated. In addition, the same analysis will be performed using the PPS as a secondary approach.

For secondary evaluation items, analysis will also be conducted using the FAS population. The mean (SD) [or median (minimum-maximum)] will be calculated for bilateral lower limb muscle strength, skeletal muscle mass, sensory impairment, range of motion, Berg Balance Scale, timed up and go test, gait parameters (step length, stride length, weight distribution, and gait speed during the 10-minute walk test), maximal oxygen uptake, and Locomo 25. Comparisons between preoperative, postintervention, and 6-month postoperative outcomes will be performed using a 1-way ANOVA or the Kruskal-Wallis test, and multiple comparisons will be conducted using the Tukey method (or Steel-Dwass test). A 2-sided significance level of 5% and a 95% CI will be used. The same analysis will also be performed using the PPS as a secondary approach.

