Furthermore, for Barthel Index (BI), Functional Independence Measure (FIM), Frenchay Activities Index (FAI), SF-36, Health Utilities Index, EQ-5D-5L (quality-adjusted life years), long-term care insurance certification level, General Self-Efficacy Scale, and WHODAS 2.0, the mean (SD) [or median (IQR)] will be calculated. Comparisons between preoperative, postintervention, and 6-month postoperative outcomes will be performed using a 1-way ANOVA or the Kruskal-Wallis test, with multiple comparisons conducted using the Tukey method (or Steel-Dwass test). A 2-sided significance level of 5% and a 95% CI will be calculated. The same analysis will be conducted using the PPS as a secondary approach.

The primary efficacy analysis will be conducted using the FAS, which includes all participants who received at least one session of HAL-assisted gait training and have at least one postintervention efficacy observation. Participants who are found to violate key eligibility criteria will be excluded from the FAS.

A secondary analysis will be performed using the PPS, which is a subset of the FAS consisting of participants who completed HAL training (5 days per week, 30 minutes per session) without any major protocol deviations and for whom the primary outcome data are available.

For missing data, a descriptive analysis will first be conducted to assess the pattern and mechanism of missingness. If the data are judged to be missing at random, multiple imputation using chained equations will be applied to handle missing values in the primary outcomes. Additionally, sensitivity analyses will be performed by comparing results between complete-case and imputed datasets to evaluate the robustness of the findings.

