### Planned Outcomes and Statistical Analysis

For the primary outcome, the 2MWD, we will compare results at 3 time points: preoperative, post intervention, and 6-month follow-up. Data will be presented as mean (SD) [or median (minimum-maximum)]. Comparisons will be performed using a 1-way ANOVA or the Kruskal-Wallis test, with a *P* value <.05 and 95% CIs reported.

Secondary outcomes will be analyzed using a similar approach. Descriptive statistics will be calculated for objective measures, like muscle strength, balance, and gait parameters, as well as for subjective scales including ADL/QOL assessments (BI, FIM, and FAI). Multiple comparisons will be conducted using the Tukey method or the Steel-Dwass test, with a *P* value <.05 and 95% CIs also reported.

For missing data, we will first conduct a descriptive analysis to assess the pattern of missingness. If the data are judged to be missing at random, multiple imputation will be applied to the primary outcomes. Sensitivity analyses will also be performed by comparing results from complete-case and imputed datasets to assess the robustness of the findings.

The primary efficacy analysis will be conducted on the FAS, and a secondary analysis on the PPS.

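### The plan does not say whether inability to walk counts as 0 m or as missing; if missing, imputation would overstate the week-8 mean, and the planned sensitivity check could not show it

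*Protocol article*

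**What the plan says.** All references are to the protocol article.

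- **Endpoint (Outcomes).** "For the primary outcome, assessment will be conducted at 8 weeks postoperatively". Table 1 describes the 2-minute walking distance (2MWD) thus: "Measures the total distance walked in 2 minutes, with pylons placed at 30-m intervals". No value is given for a patient who cannot walk.
- **Test condition (Outcomes).** At each time point, "walking ability will be assessed under standard conditions using the residual limb or temporary prosthesis, as applicable".
- **Missing data (Statistical Analysis).** The pattern and mechanism of missingness are first described. The rule for the primary outcome then reads: "If the data are judged to be missing at random, multiple imputation using chained equations will be applied to handle missing values". The Planned Outcomes and Statistical Analysis section repeats the rule: "If the data are judged to be missing at random, multiple imputation will be applied to the primary outcomes". No method is named for the case where that judgement goes the other way.
- **Robustness (Statistical Analysis).** "sensitivity analyses will be performed by comparing results between complete-case and imputed datasets". This is the only sensitivity analysis named for missing values.
- **Populations (Statistical Analysis).** The Full Analysis Set needs one HAL session and one later efficacy observation of any kind. The Per Protocol Set is limited to patients "for whom the primary evaluation item can be assessed". The Full Analysis Set has no such limit, so it can hold patients without a week-8 2MWD.

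**The concern.** Some patients may well be unable to walk at the primary visit. The Introduction says that "it takes 6-8 weeks for the stump to mature after amputation, and patients cannot bear weight on the amputated side", and the Interventions section delays the temporary prosthesis until the residual limb has matured. Week 8 therefore falls at the end of that window. The discontinuation criteria include worsening disease, adverse events and little use of the device because of postoperative complications, all of which are related to walking ability.

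Two weaknesses follow. First, a descriptive look at observed data cannot separate missing at random from missingness that depends on the unseen walking distance. Recorded reasons can inform the judgement but cannot settle it. Second, the robustness check compares two analyses that both set outcome-dependent missingness aside.

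At stake is the meaning of the week-8 mean. It could be the distance among patients able to walk, reported as the distance of all treated patients. With 20 patients and no control group, a handful of such cases matters.

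**Working it through.** The article gives no figure for missing values or for non-walkers, so there is none to reproduce. It supplies the planned N of 20 and the assumed 1.5-fold improvement, which was made for the 6-minute distance. Every share of non-walkers, mean and SD below is an assumption.

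**1. Week-8 level.** Let walkers average D metres and let k of 20 be unable to walk, so p = k/20.

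- Non-walkers scored 0 m: mean = D(1−p).
- Non-walkers missing, then dropped or imputed from walkers: mean ≈ D.
- Overstatement factor = 1/(1−p) = 20/(20−k).

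| k | p | Factor | Overstated by |
|---|---|---|---|
| 2 | 10% | 20/18 = 1.11 | 11% |
| 4 | 20% | 20/16 = 1.25 | 25% |
| 6 | 30% | 20/14 = 1.43 | 43% |

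**2. Against the assumed improvement.** Suppose that 1.5-fold holds among walkers, carries over to the 2MWD, and everyone walks before surgery. Scoring 0 m gives 1.5(1−p): 1.35-fold at 10%, 1.20-fold at 20%, 1.05-fold at 30%, and 1.00-fold (no improvement) at one third. The other two analyses still show about 1.5-fold.

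**3. Can the planned check see this?** A simulation used n = 20 and 1,500 runs per setting. Preoperative distance had mean 100 m and SD 40 m. Walkers' week-8 distance was centred on 150 m, with slope 0.6 on baseline and residual SD 60 m. Runs with no non-walker or fewer than six walkers were set aside. Imputation used baseline, by regression or by predictive mean matching (PMM). Mean week-8 distance in metres:

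| Inability related to baseline | Share unable | Scored 0 m | Complete-case | Imputed, regression | Imputed, PMM |
|---|---|---|---|---|---|
| No | 11.4% | 132.8 | 149.9 | 149.8 | 149.9 |
| No | 20.2% | 120.2 | 150.7 | 150.8 | 150.8 |
| No | 30.2% | 105.2 | 150.8 | 150.7 | 150.7 |
| No | 39.5% | 90.9 | 150.2 | 150.2 | 149.9 |
| Yes | 14.1% | 130.9 | 152.4 | 149.6 | 150.7 |
| Yes | 23.8% | 118.2 | 155.1 | 150.3 | 152.3 |
| Yes | 32.7% | 105.1 | 156.3 | 149.9 | 152.8 |
| Yes | 41.6% | 92.1 | 157.7 | 149.9 | 153.7 |

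Complete-case and imputed means differ by at most 157.7 − 149.9 = 7.8 m. Both exceed the zero-scored mean, by 17.0 m (149.8 − 132.8) up to 65.6 m (157.7 − 92.1). Close agreement between the two planned analyses therefore says nothing about this bias.

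**4. Change from baseline.** Let walkers average B metres before surgery, and let a share q be unable to walk then and be imputed in the same way.

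- Imputed change ≈ D − B.
- Zero-scored change = (1−p)D − (1−q)B.
- Difference = pD − qB.

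With B = 100 and D = 150: p = 20%, q = 0 gives +30 m; p = 20%, q = 30% gives 30 − 30 = 0 m; p = 10%, q = 30% gives 15 − 30 = −15 m. The sign depends on two unknown shares.

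**The case against.** The strongest reply is that the article never says inability is recorded as missing. A total distance of 0 m fits the Table 1 description, and if sites score it that way the imputation problem does not arise. This stands. A reader might infer that non-walkers will be imputed as walkers, but the text supports only a conditional statement. The Per Protocol Set wording makes the missing reading plausible without fixing it.

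Imputation also depends on the missing-at-random judgement. Recorded reasons such as an unhealed stump could lead the team to reject it. This stands too, although no method is then stated. The full protocol or analysis plan may hold a scoring rule or a further analysis. What does not depend on unseen documents is that the article presents the complete-case comparison as evidence of robustness, which it cannot supply.

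A reader might also infer that the bias favours the intervention. The documents do not support that for the comparison across time points, because patients awaiting amputation may be unable to walk and could be imputed as well.

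Nor does the 36% rate of successful prosthetic fitting cited in the Introduction size the problem. It comes from a geriatric vascular population, whereas entry here requires a physician's judgement that the patient has the potential to walk with a prosthesis.

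Finally, a reader might conclude that anyone without a prosthesis should count as a non-walker. The Outcomes section permits testing without one, so such a patient can have a genuine distance. An imputation model that used 6-month values might also draw lower distances than those in the table; the article does not specify the model.

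**Conclusion.** The point holds in conditional form. The article leaves open whether inability to walk is 0 m or missing. If it is treated as missing and judged missing at random, the week-8 mean level is overstated by about 1/(1−p): 11%, 25% and 43% for 2, 4 and 6 of 20. These sizes assume that all non-walkers are coded missing, are imputed near the walkers' mean, and are properly valued at 0 m. The number of non-walkers is not known. The direction of bias in the change from baseline is not established.

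The weakness of the sensitivity analysis needs no assumption about numbers. Both analyses in the comparison ignore outcome-dependent missingness, so their agreement cannot support robustness against it. The change should be made before any data are analysed. It does not call for a new primary endpoint.

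**What to change.** 1. Score the 2MWD as 0 m at any visit, including the preoperative one, where the patient cannot walk for a health or stump reason. A distance covered without a prosthesis under the permitted conditions stays as measured.
2. Record the reason for every absent value, and keep multiple imputation for values missing for unrelated reasons, such as an administratively missed visit.
3. Keep the complete-case comparison, but add a sensitivity analysis that departs from missing at random: either delta-adjusted imputation, with imputed distances lowered in steps, or missing = 0 as the extreme case.
4. Add a rank-based supporting test because of the zeros, for example a signed-rank test on within-patient changes.
5. Record whether each test was done with or without a prosthesis, and summarise the two conditions separately.

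The cost is one scoring rule, two recorded items per test, one sensitivity analysis and one supporting test. The downside is a less favourable mean and a zero-inflated distribution.

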**Figure 2 figure2:**
[figure not shown]
Flowchart for trial. HAL: Hybrid Assistive Limb (developed by Japan's Tsukuba University and the robotics company Cyberdyne).

According to the study protocol, criteria for discontinuing or modifying the allocated intervention for individual participants include the following: withdrawal of informed consent; discovery after enrollment that the participant does not meet the eligibility criteria; worsening of the primary disease that makes use of the study device inappropriate; exacerbation of comorbid conditions that hinders continuation; occurrence of adverse events that make continuation difficult; confirmation of pregnancy; significant noncompliance with study procedures; markedly low frequency of intervention use due to postoperative complications; premature termination of the entire study; or any other reason deemed appropriate by the investigator (YM, KU, and TA).

When discontinuation occurs, the reason will be explained to the participant if necessary, and postdiscontinuation care will be provided to ensure the participant is not disadvantaged.

The principal investigator (YM) considers early termination of the study in cases where the planned number of participants cannot be recruited within the designated period; the ethical review board requires protocol changes that are not acceptable; facts or information are discovered that undermine the ethical or scientific validity of the study; the integrity of the study conduct or results is compromised; or critical information emerges regarding the quality, safety, or effectiveness of the study device.

If the ethics committee recommends or instructs discontinuation, the study will be terminated accordingly. In such cases, the reason for termination will be reported in writing to the hospital director, and a study termination report will be submitted without delay. Notification will also be made to the ethics committee and the Ministry of Health, Labour and Welfare within 10 days of termination.

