### Sample Size

The calculation was performed with α=.05, a statistical power of 0.8 (80%), and an effect size of 0.8, resulting in a total sample size of 20. The target sample size includes a margin to accommodate potential dropouts. However, if the number of dropouts significantly impacts statistical power or data integrity, we plan to recruit additional participants to maintain the robustness of the analysis.

The sample size will be estimated using data from the 6-minute walk distance (6MWD), as sufficient effect size data for this outcome are available in the literature, and it is a widely recognized measure of functional walking capacity in rehabilitation research. However, performing the full 6MWD may be overly demanding for patients in the early postoperative period following limb amputation; therefore, the 2-minute walk distance (2MWD) will be selected as the primary end point. The 2MWD has been validated as a reliable and less physically demanding alternative to the 6MWD, with strong correlations reported between the two measures in neuromuscular and rehabilitation populations [13,15].

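### Imputation of the primary 2-minute walk distance is switched on only if the data are judged missing at random, a judgement the data cannot support and that is made after outcomes are in hand

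*Protocol article*

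**What the plan says.** Methods, Statistical Analysis, sets a sequence for missing data. First, "a descriptive analysis will first be conducted to assess the pattern and mechanism of missingness". Then comes the condition: "If the data are judged to be missing at random, multiple imputation using chained equations will be applied". Finally, "sensitivity analyses will be performed by comparing results between complete-case and imputed datasets". Results, Planned Outcomes and Statistical Analysis, repeats the condition: "If the data are judged to be missing at random, multiple imputation will be applied to the primary outcomes".

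Neither section gives a criterion for the judgement or says what happens to the primary analysis if it is negative. Complete cases appear only as the comparator for the imputed result.

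Missing primary values are foreseeable. To enter the Full Analysis Set (FAS) a patient needs one HAL session and must "have had at least one efficacy-related observation thereafter", which need not be the walk test. Reasons for stopping under Interventions include "markedly low frequency of intervention use due to postoperative complications" and "occurrence of adverse events that make continuation difficult", both plausibly related to walking ability.

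**The concern.** The article writes a decision rule in which a look at the data decides whether the primary outcome is imputed. Missing at random is an assumption about values nobody has seen. Comparing patients with and without a week-8 value on what was recorded can show that missingness is related to recorded variables. It cannot show whether missingness also depends on the missing value itself. The condition asks the descriptive step for something it cannot deliver.

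The choice between two primary results is then made by opinion, in a single-arm study, once the walking distances are known. A negative judgement also removes the comparison of imputed with complete-case results, because there is then no imputed dataset.

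**Working it through.** **Inputs.** From the article: 20 patients (Sample Size: "α=.05, a statistical power of 0.8 (80%), and an effect size of 0.8, resulting in a total sample size of 20"), a two-sided 5% level, and walk distance measured preoperatively, at week 8 and at month 6 (Table 2). The number 20 is taken as given; nothing here depends on how it was derived. The article gives no missing-data rate, correlation or strength of missingness. Assumed: 20% missing at week 8 (0.20 × 20 = 4 patients); log odds of being missing rising 1.5 per SD worse (odds ratio e^1.5 = 4.5); correlations 0.5 (preoperative with week 8), 0.5 (preoperative with month 6) and 0.8 (week 8 with month 6).

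**Step 1: what can the descriptive look detect?** Two-sample t test of the preoperative value, missing versus observed, true difference d = 0.8 SD:

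- noncentrality = d × √(n₁n₂/(n₁+n₂)) = 0.8 × √(4 × 16/20) = 0.8 × 1.789 = 1.431
- critical value, 18 degrees of freedom = 2.101
- power = 0.27

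With 3 versus 17 the power is 0.23, and with 5 versus 15 it is 0.31.

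A second simulation used 20 patients, about 20% missing, log odds rising 1.0 per SD, and missingness driven by the unseen week-8 value. The same comparison was significant in 6%, 7%, 12% and 19% of trials at preoperative to week-8 correlations of 0, 0.3, 0.5 and 0.7. Even a significant result would be compatible with either mechanism.

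**Step 2: what is lost if imputation is skipped although missingness depends on recorded values?** Simulation of 1,000,000 records from a trivariate normal distribution. Bias of the week-8 mean, in SD:

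| Missingness driven by | Observed values only | Imputed from preoperative and month-6 values |
|---|---|---|
| Preoperative value | 0.11 | 0.00 |
| Observed month-6 value | 0.18 | 0.00 |

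Both cases are missing at random given the recorded visits. The bias enters only if the judgement goes the wrong way, and Step 1 shows how little there is to guide it.

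**Step 3: what if missingness depends on unseen values?** Same assumptions; bias in SD, observed values only versus imputed:

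| Missingness driven by | Month 6 | Week-8 mean | Change from baseline |
|---|---|---|---|
| Week-8 value | available | 0.23 vs 0.09 | 0.11 vs 0.09 |
| Week-8 value | also missing | 0.23 vs 0.18 | 0.11 vs 0.18 |
| Change | available | 0.11 vs 0.09 | 0.23 vs 0.09 |
| Change | also missing | 0.11 vs 0.18 | 0.23 vs 0.18 |

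Neither method is free of bias. With month 6 available, imputation is less biased in every cell. With month 6 also missing, the order reverses in two of four cells.

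**Step 4: does the planned sensitivity analysis cover this?** It compares complete cases with values imputed under missing at random. Neither lets the missing patients be worse than their recorded data predict, so agreement between the two says nothing about that possibility.

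**The case against.** The strongest defence is that the article is a condensed account and the full protocol or analysis plan may define the negative branch. That is fair, and the gap alone would not be a finding. The point rests on the condition, which is printed in two sections and would remain unsound whatever else is written.

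A reader might infer that complete-case analysis is the plan's fallback, and that the rule therefore picks the more biased method exactly when data are not missing at random. The documents do not support the first part: complete cases are named only as a sensitivity comparator. Nor is the second generally true, as Step 3 shows. A ratio of about 2.5 (0.23/0.09) arises for the week-8 mean when month 6 is observed for every patient missing week 8. On change from baseline the figures are 0.11 and 0.09, and when month 6 is missing too they become 0.11 and 0.18.

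Other mitigating facts stand. Patients remain in hospital until the week-8 evaluation, so gaps may be few. The study calls itself exploratory and provides for extra recruitment. Where imputation is done, both results will be compared. There is no allocation to unblind, and whoever judges could confine the look to covariates and withdrawal reasons, although the article does not require that. These facts limit the exposure but do not make the judgement testable.

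**Conclusion.** The concern holds in a limited form. The primary handling of missing data depends on an untestable judgement, made with outcomes available and without a stated criterion. The check behind it has about 27% power for a 0.8 SD baseline difference with 4 of 20 values missing. A mistaken refusal to impute would bias the week-8 mean by about 0.11 to 0.18 SD under the assumed missing rate, strength of missingness and correlations; with fewer missing values or weaker dependence the bias would be smaller. No claim is made that complete-case analysis is uniformly worse when data are missing not at random. It is worth correcting before analysis, but it does not invalidate the design.

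**What to change.** In Methods (Statistical Analysis) and Results (Planned Outcomes and Statistical Analysis), delete the condition on missing at random. State that the primary FAS analysis always uses multiple imputation by chained equations, with the patient's 2-minute walk distance at other visits and baseline data in the imputation model. Keep complete cases as a sensitivity analysis only, and keep the description of missingness as a report that does not choose the method.

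Add a simple delta-adjusted sensitivity analysis: lower the imputed week-8 values by a prespecified series of amounts and report where the conclusion changes. With 20% missing, lowering them by δ SD moves the week-8 mean by 0.20 × δ SD, so 0.5 SD moves it by 0.10 SD.

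The cost is a sentence or two in each section and a little more analysis work. No new data are needed, and the planned test need not change.
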